### Economic evaluation

The economic evaluation will take on a societal perspective, including both costs to the health system and patient out-of-pocket costs. It will model the potential cost-effectiveness of routine infant vitamin D supplementation compared to no supplementation, assuming Australia-wide implementation. The evaluation will assess the differential impact of supplementation on primary trial outcomes at 12 months compared with no supplementation. Costs associated with the intervention and use of healthcare services including hospital presentations and admissions, outpatient visits, visits to specialists and other providers (including alternative providers) and medications will be collected at 6 and 12 months to specifically capture costs associated with allergic symptoms that may arise in both groups. We will supplement this data by linking to the Australian Pharmaceutical Benefits Scheme (PBS) and the Medical Benefits Scheme (MBS) to obtain costs of pharmaceuticals and Medicare health service utilisation. This data will enable us to collect information about specialist visits, GP visits and medications-related costs for children with the primary and secondary outcomes identified in the study, including LRIs. This will be supplemented by costing data from the Royal Children's Hospital for inpatient and outpatient stays, in addition to the parent questionnaire from which we will gather out-of-pocket costs for time off work, caregiver time and travel time to appointments.

Results will be presented in terms of cost per case of food allergy averted. A sensitivity analysis will assess the robustness of results to the uncertainty of model parameters. We will model the longer term costs and effects of primary trial outcomes beyond the horizon of the trial; drawing from published literature, with the potential to extend the analysis to secondary outcomes determined to be clinically important as the trial progresses and related diseases, including bone health.

### Statistical analysis

Outcomes will be compared between the vitamin D and the placebo groups using an intention-to-treat analysis. For all outcome measures, the magnitude of between-group differences will be quantified by calculating estimated OR with 95% CI for the corresponding population OR. As a secondary analysis, the analysis will be repeated in the ‘per protocol’ (infants breastfed for at least 6 months and fully compliant with the randomisation and on the basis of 25OHD3 levels achieved). Further analyses using multivariable logistic regression will be undertaken to explore the sensitivity of the estimated ORs to covariate imbalance between the groups due to potential confounding factors introduced postrandomisation, such as age of onset of formula feeding. While the design mitigates very strongly against covariate imbalance between the trial arms, colleagues have recently shown that post hoc adjustment of the intervention–outcome association for such imbalances can, under some circumstances, maintain unbiased estimates while reducing their SE.^25^ Linear regression will be used for non-categorical variables.

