**Methods nd analysis:**

Infants (n=3012) who are fully breastfed and not receiving vitamin D supplementation will be recruited at the time of their first immunisation, from council-led immunisation clinics throughout metropolitan Melbourne, Australia. The primary outcome is challenge-proven food allergy at 12 months of age. Secondary outcomes are food sensitisation (positive skin prick test), number of lower respiratory infections (through hospital linkage), moderately-severe and persistent eczema (by history and examination) and vitamin D deficiency (serum vitamin D <50 nmol/L) at age 12 months. The trial is underway and the first 130 participants have been recruited.

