### Outcomes

*Primary*
Challenge-proven food allergy at 12 months of age.

*Secondary*
Number of LRIs by 12 months of age;Food sensitisation (positive skin prick test) at 12 months of age;Moderately-severe and persistent eczema at 12 months of age;Vitamin D deficiency at 12 months of age.

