### Sample size

A final sample size of 1205 infants in each group (2410 total), will enable us to identify a 30% reduction in food allergy with 80% power (based on a two-sided test with α=0.05). A 30% reduction in the prevalence of food allergy attributed to vitamin D supplementation represents a clinically important reduction on a population level. Assuming 80% follow-up at 12 months of age, we plan to recruit a total of 3012 participants over 3.5 years (approximately 79 per month).

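### The number of LRIs is a count: the blanket OR rule fits it only if it is cut to any/none, and linear regression uses no observed time

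*Protocol article*

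**What the plan says.** All references are to the protocol article.

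- **Statistical analysis** sets one effect measure: "For all outcome measures, the magnitude of between-group differences will be quantified by calculating estimated OR with 95% CI". Its last sentence adds "Linear regression will be used for non-categorical variables". Logistic regression is named for the adjusted analyses. No count model, rate ratio, risk ratio or risk difference is named.
- **Outcomes** lists "Number of LRIs by 12 months of age" as a secondary outcome. The Abstract also words it as a count: "number of lower respiratory infections (through hospital linkage"). No any/none form is defined anywhere.
- **Outcomes** gives a binary primary outcome: "Challenge-proven food allergy at 12 months of age".
- **Sample size** states "A final sample size of 1205 infants in each group (2410 total") and that this "will enable us to identify a 30% reduction in food allergy with 80% power". The next sentence describes that target as a reduction in prevalence.
- **Economic evaluation** states: "Results will be presented in terms of cost per case of food allergy averted".

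**The concern.** The two sentences in Statistical analysis give different instructions for the LRI count. The first requires an OR for every outcome, so the count has to be dichotomised at a cut-point that the article does not state. The second sends any non-categorical variable to linear regression, which yields a difference in means and no OR. Two analysts could follow the section faithfully and report different LRI effects, one on the proportion ever infected and one on the mean number of infections.

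If the OR sentence governs, an infant with three infections counts the same as an infant with one, and power falls. If the linear sentence governs, power is kept, but the result has no rate-ratio form and infants observed for different lengths of time are treated alike.

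A smaller, related matter concerns the binary outcomes. The design target is a relative fall in prevalence and the economic result needs an absolute one. The OR is neither.

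**Working it through.** **1. The plan's own figure.** The control prevalence of food allergy is not stated in the article, so 1205 per group cannot be reproduced from stated inputs alone. With RR 0.70, two-sided α = 0.05 and 80% power, the usual two-proportion formula is

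n = [1.96·√(2p̄(1−p̄)) + 0.84·√(p1(1−p1) + p2(1−p2))]² / (p1−p2)².

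At an assumed p1 = 0.11 and p2 = 0.077 it gives n = 1221, and power at 1205 is 79.5%. Solving for n = 1205 gives p1 = 11.1% (11.6% with continuity correction). Recruitment is 2410/0.80 = 3012.5, which matches 3012. The sample size is therefore consistent with a risk ratio of 0.70 at a prevalence near 11%.

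**2. Power for LRIs: whole count against any/none.** From the document: n = 1205 per arm. Assumed, because the article gives no LRI rate: control mean μ1 from 0.05 to 1.0 per infant, μ2 = 0.8·μ1, negative binomial dispersion k = 0.5, 1 or 2, and full follow-up.

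- Rate model: Var(log rate ratio) = [(1/μ1 + k) + (1/μ2 + k)]/n; power = Φ(|ln 0.8|/SE − 1.96).
- Any/none: P(any) = 1 − (1 + kμ)^(−1/k), then two-proportion power.
- Difference in means: Var = [(μ1 + kμ1²) + (μ2 + kμ2²)]/n.

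Worked case, μ1 = 0.4 and k = 1:

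- Rate model: (3.5 + 4.125)/1205 = 0.00633, SE = 0.0795; 0.2231/0.0795 − 1.96 = 0.85; power 80%.
- Any/none: 28.6% against 24.2%; power 67%.
- Difference in means: (0.56 + 0.4224)/1205 = 0.000815, SE = 0.0286; 0.08/0.0286 − 1.96 = 0.84; power 80%.

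| Control mean | Rate model, k = 0.5 / 1 / 2 | Any/none, k = 0.5 / 1 / 2 | Points lost (approx.) |
|---|---|---|---|
| 0.05 | 21 / 20 / 20% | 20 / 20 / 19% | 1 |
| 0.1 | 36 / 35 / 32% | 34 / 32 / 29% | 2 to 3 |
| 0.2 | 60 / 57 / 51% | 55 / 50 / 43% | 5 to 8 |
| 0.4 | 85 / 80 / 70% | 76 / 67 / 54% | 9 to 17 |
| 1.0 | 99 / 96 / 87% | 90 / 78 / 57% | 9 to 30 |

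Simulation (2,000 trials per setting, same n and rate ratio) agrees. At mean 0.5 and k = 1, power is 86% for the rate ratio, 86% for the difference in means and 70% for any/none. At mean 1.0 and k = 1 it is 97%, 97% and 78%. Coverage of the difference in means with an unequal-variance standard error was 94 to 96%.

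**3. Observed time.** Start of the study reports 13% drop-out at a mean of 5.9 weeks after recruitment; Table 2 gives a mean entry age of 7.4 weeks. Planned follow-up is about 52 − 7.4 = 44.6 weeks. These infants contribute about 0.13 × 5.9/44.6 = 1.7% of planned person-time.

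**4. OR against RR for the primary outcome.** OR = RR(1−p)/(1−RR·p). At p = 0.111: 0.70 × 0.889/(1 − 0.0777) = 0.67. The absolute reduction is 0.30 × 11.1% = 3.3 points.

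**The case against.** **The two sentences can be read together.** The closing sentence can be taken as qualifying the first: ORs for categorical outcomes, linear regression for the rest. That is the more natural reading, and the article never proposes an any/none LRI outcome. On it there is no power loss under full follow-up. This stands, so a reader who infers that the trial will lose up to 30 points of power goes too far. The loss follows only from applying the OR sentence literally, and its upper end needs a mean of 1.0, at which 42 to 56% of control infants would have an LRI. The Discussion calls the outcomes of interest low in prevalence, which points towards the smaller losses.

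**Drop-out may matter little.** A reader might infer that early leavers seriously distort the LRI count. The documents do not support that. Those infants hold under 2% of planned person-time, and LRIs are also sought from GP and hospital records, which may recover their events; whether withdrawn infants stay linked is not stated. The 13% is also an early figure from 130 infants. The offset is good practice here but would recover little from these leavers.

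**The OR is a valid measure for a binary primary outcome.** It is, and 0.67 against 0.70 changes neither the test nor the conclusion. A reader might infer that the OR must be replaced; that would be a preference. Cases averted can also be derived from the arm prevalences, and Economic evaluation is not restricted to ORs. What remains is a case for reporting the absolute and relative risks as well.

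**Model detail usually sits in an SAP.** True of the count model and offset. But the article itself fixes an OR for all outcomes, and an SAP would have to override that for LRIs.

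Nor do the documents rank LRIs above the other secondary outcomes: Outcomes lists them first, while the Abstract lists food sensitisation first.

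**Conclusion.** The point holds as a defect of specification for one secondary outcome. The OR rule as written cannot be applied to the number of LRIs without an undefined dichotomy, and it conflicts with the linear-regression sentence in the same section. If the count were dichotomised, the power lost would run from about 1 point at a mean of 0.05 to as much as 30 points at a mean of 1.0. All of these figures depend on assumed LRI means, dispersions and a 20% reduction. If linear regression is used, power is preserved and, with robust standard errors, the difference in means is valid; the shortcomings are the missing rate ratio and the unused observed time.

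For the binary outcomes, the mismatch with the design and economic scales is a reporting matter, small for food allergy. The primary test and the sample size are unaffected.

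**What to change.** Three changes to the analysis wording, made before unblinding:

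1. Limit the OR sentence to binary outcomes.
2. Analyse the number of LRIs with a negative binomial model, or Poisson with robust standard errors, with log(observed time) as offset. Report a rate ratio with 95% CI, and state what counts as observed time when events come from records as well as questionnaires.
3. For binary outcomes, report the risk difference and risk ratio with 95% CI alongside the OR, and use the risk difference for cost per case averted.

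The cost is this wording and a few lines of code. No visit, procedure or recruitment target changes.

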### Intervention

Infants will be randomly assigned to receive 400 IU vitamin D3-Cholecalciferol (1 drop, 0.03 mL) (Baby D drops) or an identical placebo (1 drop vegetable oil) daily until 12 months of age. Both active and placebo interventions will be supplied by the D Drops Company, Ontario, Canada which currently provides the active product commercially under the regulation of Health Canada's Natural Health Product Directorate.

The current daily dose recommended for infants in the first year of life is 400 IU in all available published international guidelines; USA^18^ and UK National Health Service (NHS) guidelines. A daily dose of 400 IU administered from around 4 weeks of age was sufficient to increase vitamin D levels to ≥50 nmol/L in 98% of infants by 3 months of age.^19^

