### Compliance

We have developed an iPhone application to remind study participants to give their infant the study medication and to monitor dosing compliance. This information can be emailed from the app to [contact] and incorporated into the REDCapdatabase. An android-based application is in development. For participants without smart phones, a paper diary system is available. These can be sent back via mail or photographed and emailed. Participants are asked to send their empty bottles of study medication to the Clinical Trials Pharmacy for re-weighing to measure compliance with daily dosing. To date compliance with daily dosing is 90% based on the number of returned, completed diaries.

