### Data collection

Table 1 summarises timing of measures, described in more detail below. Web-based questionnaires will be administered to parents at baseline and when their infant is aged 3, 6, 9 and 12 months. Infants will be invited in for a clinical assessment, blood sample and allergy testing at age 12 months at the completion of the intervention. An optional RCH clinic visit at age 6 months will be offered to participants and will include an eczema examination and blood draw. Daily diaries will be used to record compliance with drug dosing, changes to infant feeding, new allergy symptoms, medication use and medical visits to inform the economic evaluation.

**Table 1 BMJOPEN2015009377TB1:** Summary and timing of measures

[figure not shown]

SCORAD, Scoring of Atopic Dermatitis; SPT, skin prick test.

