*Parent Questionnaire (3 monthly)*: To capture dietary vitamin D intake and environmental UV radiation (UVR) exposure, we will ask questions about maternal vitamin D supplements, infant diet, maternal and infant sun exposure and sun protective behaviours as in our previous work,^15^ for example, number of hours spent in the sun per day, during summer or winter, weekends and holidays, will be collected for mother and child. Cumulative UVR dose will be calculated as the product of time spent outdoors and ambient UVR during the period. Composite skin exposure and sun protection indices will be measured. We have established that composite maternal UVR dose (OR 0.50 (95% CI 0.37 to 0.69) p<0.001) and maternal skin exposure index (OR 0.81 (95% CI 0.66 to 0.98) p=0.03) were associated with breastfed infant vitamin D status but infant time in the sun during the first year was not.^15^ Infant feeding (amount of breastfeeding, formula feeding and type of formula, introduction of solid foods) will also be recorded. At 12 months only, infant skin/hair/eye colour will be assessed using a standardised, validated chart. We have validated that the charts predict (p<0.001) skin melanin density by spectrophotometer.^24^

*Blood samples (12 months)*: Peripheral blood mononuclear cells will be separated from whole blood and stored in liquid nitrogen, and plasma will be stored and frozen in our −80°C freezer. These will be retained for future analysis to evaluate immune function including regulatory T cell and cytokine assays.

*Newborn screening (Guthrie) card*: consent will be obtained at recruitment to access Guthrie cards to undertake assessment of vitamin D levels at birth.

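### The secondary per-protocol set is selected partly on achieved 25OHD3, a treatment-affected trial outcome, so its two arms are not comparable

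*Protocol article*

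**What the plan says.** The Statistical analysis section of the protocol article sets the main comparison: "Outcomes will be compared between the vitamin D and the placebo groups using an intention-to-treat analysis". It quantifies differences by ORs for all outcome measures. It then repeats the analysis, labelled secondary, in a per-protocol set described as "infants breastfed for at least 6 months and fully compliant with the randomisation and on the basis of 25OHD3 levels achieved". No cut-off is given, and nothing says whether the level criterion works the same way in both arms.

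Four other places describe the selection variable:

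- Intervention: in a cited study the trial's daily dose "was sufficient to increase vitamin D levels to ≥50 nmol/L in 98% of infants by 3 months of age".
- Outcomes: the secondary outcomes include "Vitamin D deficiency at 12 months of age", which the Abstract defines as serum vitamin D below 50 nmol/L.
- Data collection: "Infants will be invited in for a clinical assessment, blood sample and allergy testing at age 12 months at the completion of the intervention". The 6-month clinic visit with a blood draw is optional.
- Secondary outcomes, three-monthly questionnaire: maternal UV dose and maternal skin exposure "were associated with breastfed infant vitamin D status but infant time in the sun during the first year was not".

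**The concern.** A per-protocol set should be chosen by whether the assigned treatment was taken. Here it is also chosen by a result of treatment. On active drops, almost any infant who takes them will pass a level criterion. On placebo, an infant passes because of the mother's sun exposure, formula, or supplements from outside the trial. A single level criterion therefore selects on different characteristics in each arm, and randomisation no longer protects the comparison.

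The article's own Introduction says that low vitamin D goes with more food allergy. If background determinants of vitamin D status also relate to allergy risk, the per-protocol OR can move away from 1 when the drops do nothing. For vitamin D deficiency the problem is more direct, because the set is selected on the variable that defines the outcome.

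**Working it through.** **Step 1. Deficiency outcome.** The only assumption is that the level criterion uses the article's own deficiency threshold of 50 nmol/L.

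- At least 50 required in both arms: no deficient infants in either arm, so the OR is undefined (0/0).
- Active at least 50, placebo below 50: 0% against 100% deficient, so the OR is 0 by construction.
- At least 50 required in the active arm only: 0% deficient on active by construction, so the OR is 0 as long as any placebo infant is deficient.

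No reading yields information about the drops.

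**Step 2. Food allergy with a true OR of 1.** The article reports no figure for this, so there is none to reproduce, and it gives no control-arm allergy rate. I use 11.13%, the rate implied by its sample size. With p1 = 0.1113, p2 = 0.7 × 0.1113 = 0.0779 and mean 0.0946:

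n = [1.960 × √(2 × 0.0946 × 0.9054) + 0.842 × √(0.1113 × 0.8887 + 0.0779 × 0.9221)]² / 0.0334² ≈ 1205 per group, the stated number.

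The remaining inputs are assumptions:

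- Mean 25OHD3 is 55 nmol/L on placebo and 85 on active, with SD 20.
- A share f of infants (15 to 25%) has a background trait that lowers the level by d (10 to 15 nmol/L).
- The trait multiplies the odds of allergy by 2.0 to 3.5.
- The cut-off is 50.

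*Stronger corner: f = 0.25, d = 15, allergy OR 3.5.*

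Risks are 0.0748 without the trait and 0.2207 with it (check: 0.75 × 0.0748 + 0.25 × 0.2207 = 0.1113).

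Probability of reaching 50:
- Active: Φ(35/20) = 0.960 without the trait, Φ(20/20) = 0.841 with it.
- Placebo: Φ(5/20) = 0.599 without the trait, Φ(−10/20) = 0.309 with it.

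Risk in a subset = 0.0748 + (trait share) × 0.1459.

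| Subset | Retained | Trait share | Risk | Odds |
|---|---|---|---|---|
| Active ≥50 | 0.75×0.960+0.25×0.841 = 93.0% | 0.226 | 0.1078 | 0.1208 |
| Placebo ≥50 | 0.75×0.599+0.25×0.309 = 52.6% | 0.147 | 0.0962 | 0.1064 |
| Placebo <50 | 47.4% | 0.365 | 0.1280 | 0.1468 |
| Placebo, all | 100% | 0.250 | 0.1113 | 0.1252 |

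Per-protocol ORs:
- Active ≥50 against placebo <50: 0.1208/0.1468 = 0.82.
- At least 50 in both arms: 0.1208/0.1064 = 1.14 (1.135 before rounding).
- Cut-off in the active arm only: 0.1208/0.1252 = 0.96 (0.965 before rounding).

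*Milder corner: f = 0.15, d = 10, allergy OR 2.0.* Risks are 0.0991 and 0.1804. Trait shares are 0.141 (active ≥50), 0.106 (placebo ≥50) and 0.208 (placebo <50). Subset risks are 0.1106, 0.1077 and 0.1160. The three ORs are 0.95, 1.03 and 0.99.

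*Trait reversed: f = 0.20, d = 12, allergy OR 0.5.* Risks are 0.1228 and 0.0654. Trait shares are 0.186, 0.132 and 0.284. Subset risks are 0.1121, 0.1152 and 0.1065. The three ORs are 1.06, 0.97 and 1.01.

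Simulation over the same assumed ranges agrees closely: 0.83 to 0.94, 1.03 to 1.14 and 0.97 to 1.01 for the three readings.

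**Step 3. Sensitivity to the model.** A different model takes the 98% from the Intervention section for the active arm and lets 50 to 90% of placebo infants reach 50. It assumes a prognostic factor correlated 0.7 with 25OHD3, with an allergy OR of 1.2 or 1.5 per SD. The ranges become 0.62 to 0.90, 1.02 to 1.25 and 0.98 to 0.99. The pattern across readings is the same, but the sizes are not.

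**The case against.** The best defence has four parts.

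**It is a secondary analysis.** Intention-to-treat is the main comparison, and neither the sample size nor the economic evaluation is tied to the per-protocol set. This stands, and it limits the severity.

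**The exact rule may be in the full protocol or SAP.** The missing cut-off is indeed no finding. But any cut-off in either arm selects on a level that treatment moves, so detail elsewhere would not cure the rule. The wording could mean that compliance is judged by level, but then the level still decides who is kept.

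**The bias may be small, and its inputs are assumed.** A cut-off in the active arm only gives almost no bias for food allergy, and the article supplies none of the distributions used above. Both points stand. They leave the size and direction open, not the differential selection or the circular deficiency result.

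**Confounders are measured.** Ancestry, sun exposure and skin colour are collected, and multivariable models are planned. The article does not say those models apply to the per-protocol set, and they could not repair the deficiency comparison.

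A reader might also infer more than the article supports:

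- *That the analysis will show a false benefit.* Only one reading of the rule does so, and only if the confounder runs in the assumed direction. Nor does the article suggest that this analysis would be favoured if intention-to-treat were null.
- *That the 6-month breastfeeding filter also unbalances the arms.* It is a post-randomisation criterion, but parents and staff are blinded and the placebo is identical, so duration should be nearly balanced. A simulation of this filter alone gave an OR of 1.006, within simulation error of 1.
- *That the compliance data are invalid.* The interim figure discloses its basis ("To date compliance with daily dosing is 90% based on the number of returned, completed diaries"), and no analysis is said to use it. The bottle instruction ("Participants are asked to send their empty bottles of study medication to the Clinical Trials Pharmacy for re-weighing to measure compliance") may simply be loose wording for used bottles, since re-weighing makes sense only if some contents may remain.

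**Conclusion.** The concern holds for the 25OHD3 criterion alone. Selecting the per-protocol set on achieved 25OHD3 conditions on a post-randomisation result that the intervention raises and that defines a secondary outcome. The retained arms are not comparable, and the per-protocol OR for vitamin D deficiency is circular.

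For food allergy with no true effect, the OR is about 0.83 to 0.94, 1.03 to 1.14, or 0.97 to 1.01, depending on the unstated cut-off rule. The direction reverses if the confounder works the other way. These figures rest on assumed 25OHD3 distributions, confounding and control risk. They illustrate the problem and do not predict this trial's result. The differential selection itself does not depend on them.

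The intention-to-treat result is not affected. This should be fixed, but it does not threaten the trial's primary conclusion.

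**What to change.** Before unblinding, in the protocol and SAP:

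1. Delete the achieved-25OHD3 criterion from the per-protocol definition.
2. Define compliance by doses given, with the same rule in both arms.
3. Report 25OHD3 by arm only as the secondary outcome it already is.
4. Optionally, add a complier-average estimate with randomised arm as the instrument, as a supportive analysis. It needs its own assumptions and must deal with supplements taken outside the trial, which the Discussion already anticipates in the placebo group.

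The timing matters because choosing a cut-off after unblinding would amount to choosing the direction of any bias.

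The cost is a few lines of text. The drawback is that the per-protocol set loses its biochemical check of compliance. Selection on doses given is still selection after randomisation, so the per-protocol result should remain supportive.

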### Inclusion and exclusion criteria

*Inclusion criteria*: Healthy, term, breastfeeding 6–8 week old infants. Infants of mothers who intend to continue predominantly breastfeeding until 6 months will be recruited since formula feeding is a surrogate form of partial vitamin D supplementation.

*Exclusion criteria*: Infants with the following will be excluded: already receiving vitamin D supplementation, born premature (<37 weeks)/low birth weight (<2500 g), multiple births, poor health due to a current or past significant disease state or congenital abnormality or infants on medication that interfere with vitamin D metabolism. Mothers who receive antenatal vitamin D supplementation will not be excluded because in our setting, this has not been shown to be protective against postnatal infant vitamin D deficiency.^15^

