## Discussion

The results of the VITALITY trial will determine whether vitamin D supplementation has a role in optimising infant immune health in the first year of life, reducing the risk of allergic disease and respiratory diseases. Furthermore findings will provide evidence to inform guidelines for vitamin D supplementation of infants. This will be the first population-based trial of postnatal infant vitamin D supplementation sufficiently powered to address the impact on any disease outcome including allergic disease, LRIs and bone health.

The strengths of VITALITY are that it is a large preventative, population-based trial thus the results are more likely to be generalisable. Another strength is that VITALITY will examine multiple important outcomes including food allergy and lower respiratory infections. Furthermore we are uniquely placed internationally to assess the role of vitamin D in early life development since Australia does not currently recommend universal infant vitamin D supplementation and is one of the few countries where there is no routine fortification of the food chain supply.

A logistic issue for VITALITY is that the trial needs to be large and thus costly, as the outcomes of interest are low in prevalence. Restricting the trial to infants with vitamin D deficiency would require a smaller trial, however it would be unethical to randomise these infants to placebo thereby not treating with vitamin D. The use of vitamin D supplements in the placebo group is another potential issue however we are collecting sufficient data regarding feeding practices, supplement use and sun exposure to account for this.

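### The planned sensitivity analysis adjusts the randomised odds ratio for post-randomisation factors, which cannot confound it and which can distort it if allocation affects them

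*Protocol article*

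**What the plan says.** The main comparison is clear: "Outcomes will be compared between the vitamin D and the placebo groups using an intention-to-treat analysis". After a secondary per-protocol analysis, the Statistical analysis section adds a third layer: "Further analyses using multivariable logistic regression will be undertaken to explore the sensitivity of the estimated ORs to covariate imbalance". The imbalance in question is "covariate imbalance between the groups due to potential confounding factors introduced postrandomisation, such as age of onset of formula feeding". The reason given is that "post hoc adjustment of the intervention–outcome association for such imbalances can, under some circumstances, maintain unbiased estimates while reducing their SE". The section does not restrict adjustment to baseline variables, and it attaches no causal assumption or caveat to the post-randomisation ones.

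Two other places bear on the named example. The inclusion criteria explain that "formula feeding is a surrogate form of partial vitamin D supplementation", so formula is part of the exposure under study. The three-monthly parent questionnaire records infant feeding during follow-up, so formula started after enrolment is measured after allocation.

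**The concern.** Confounding of a treatment comparison needs a common cause of treatment and outcome. Allocation here is by a randomisation schedule, so nothing that happens later can be a cause of it. The plan calls such later factors confounders and proposes to adjust for them as a check on the randomised result.

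This matters because a check of this kind is read as evidence about robustness. If the adjusted odds ratio differs from the crude one, a reader may doubt a sound intention-to-treat result, or may prefer an adjusted estimate that randomisation no longer protects.

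**Working it through.** **1. Where an arm difference in formula timing could come from.**

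- *Chance.* The factor then behaves like a baseline covariate. Adjustment does little harm, but there is no confounding to remove, and the absence of an arm effect has to be assumed.
- *A consequence of allocation.* Conditioning on the factor blocks any effect that passes through it. If it also shares an unmeasured cause with food allergy, such as atopic tendency, conditioning opens a collider path.
- *Differential loss to follow-up.* This is a missing-data problem, which adjustment for feeding does not in general solve.

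**2. Whether the second source is possible here.** The Objectives include a reduction in eczema, and the Introduction says food allergy and infant eczema go together. If parents change feeding in response to eczema (my assumption; the article does not say so), the trial's own hypothesis makes formula timing depend on arm. Blinding does not close this route, because it runs through symptoms and not through knowledge of allocation.

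**3. Illustrative size.** The article attaches no figure to this analysis, so there is none to reproduce, and every input here is assumed. With Z = arm, M = early formula and Y = food allergy, the crude model is logit P(Y) = a + bZ and the adjusted model is logit P(Y) = a + bZ + cM. Each scenario used 2,000,000 simulated infants.

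| Scenario | M by arm | Crude OR | Adjusted OR |
|---|---|---|---|
| No effect; M unaffected by arm | equal | 0.99 | 0.99 |
| No effect; M affected, shared cause with Y | 37% vs 48% | 1.00 | 0.93 |
| As above, stronger | 40% vs 57% | 1.00 | 0.84 |
| Effect acts only through M | 35% vs 55% | 0.84 | 1.00 |
| True effect; M unaffected | 37% vs 37% | 0.695 | 0.694 |
| True effect; M raised by arm | 37% vs 48% | 0.69 | 0.64 |
| True effect; M lowered by arm | 37% vs 27% | 0.70 | 0.75 |

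The fourth row can be checked by hand. M was 0.354 and 0.55 by arm, and allergy risk was 0.0649 and 0.0553. The crude OR is (0.0553/0.9447) / (0.0649/0.9351) = 0.0585/0.0694 = 0.84. If M is the only route, the change in risk with M is (0.0553 − 0.0649)/(0.55 − 0.354) = −0.049. Risk without early formula is then 0.0649 + 0.354 × 0.049 = 0.082, and with it 0.082 − 0.049 = 0.033, the same in both arms. Within each level of M the OR is 1.00, so adjustment erases the whole real effect.

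**4. Precision.** Rescaled to 2410 infants, the SE of the log OR was 0.137 crude and 0.139 adjusted in the second row, and it did not fall in any scenario. The second-row shift is ln(0.93) = −0.073, about half of that SE.

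**5. Crude against adjusted as a test of imbalance.** With perfectly balanced baseline covariates (assumed ORs 6.0, 2.0 and 1.6), the treatment OR moved from 0.69 to 0.66 and the SE rose 6%. For an outcome of about 50% prevalence, the OR moved from 0.72 to 0.68 and the SE rose 9%. Nothing was imbalanced; the gap is non-collapsibility of the odds ratio. A gap between the two ORs is therefore not a clean sign of imbalance.

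**The case against.** Much can be said for the plan.

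- **Rank of the analysis.** It is a further analysis. No sample size or decision rule in the article depends on it. A reader might infer that the trial's main result is compromised; it is not, because the intention-to-treat comparison stands apart. This stands in full.
- **Bias needs an arm effect on formula timing.** The trial is double-blind with an identical placebo, and nothing in the article reports such an effect. In Table 2, 36 of 100 infants with data already had some formula, started at a mean of 2.5 weeks against a mean enrolment age of 7.4 weeks. For most of them onset preceded allocation. This limits the likely size. It does not rescue the rationale, because for the other 64% any onset comes later and the text itself calls the factor post-randomisation.
- **The simulated inputs are strong.** In a separate set-up with no true effect and about 10% prevalence, arm shifts in formula timing of 0.08, 0.16, 0.25 and 0.35 SD moved the OR to about 1.04, 1.07, 1.12 and 1.18 away from the null. That assumed a correlation of 0.57 between timing and atopic tendency. With 1205 per arm, the chance SE of an arm difference is √(2/1205) = 0.041 SD, so these shifts are about 2 to 9 SEs. At a correlation of 0.2, the first two shifts moved the OR by only 1.5 to 3.5%. No figure can be taken as the expected bias.
- **The precision claim.** A reader might infer that the statement "maintain unbiased estimates while reducing their SE" is simply false. It is hedged by its reference to certain circumstances, and the plan also has linear models, where prognostic adjustment does reduce the SE. Even in the logistic examples, power rises: ln(0.66)/ln(0.69) = 1.12, and 1.12/1.06 gives z about 6% higher; ln(0.68)/ln(0.72) = 1.17, and 1.17/1.09 gives about 8% higher. What remains is that this argument belongs to baseline covariates.
- **The Discussion.** On supplement use in the placebo group it says "we are collecting sufficient data regarding feeding practices, supplement use and sun exposure to account for this". A reader might take this as a second commitment to post-randomisation adjustment. It names no model, and a description by arm would satisfy it.

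**Conclusion.** The concern holds as a defect in a stated supporting analysis and should be corrected. The factors named cannot confound the randomised comparison, and the justification offered fits a different class of covariate. Whether adjustment would bias the result depends on whether allocation shifts formula timing, which the article neither shows nor rules out. If it does, the error can go in either direction, including removal of a real effect. If it does not, the adjustment has no confounding to correct. The simulated values show direction and mechanism only. The primary analysis and the sample size do not change.

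**What to change.** In the Statistical analysis section, replace adjustment for factors introduced after randomisation with one adjusted analysis limited to baseline covariates fixed in advance, not chosen by observed imbalance. Suitable ones are already collected, for example family history of allergy, parental ancestry, sex, siblings, baseline SCORAD and formula use at enrolment. State that the odds ratio from this model may differ from the crude one even under perfect balance.

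Report later formula feeding by arm. Any analysis that involves it should be labelled exploratory and use a causal method, such as mediation analysis, with its assumptions stated. It should not be presented as confounder control or as a robustness check of the intention-to-treat result. A ban on such analyses is not needed, since formula is a partial source of the exposure under study.

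The change is wording only and needs no new data. What is lost is the analysis now described as control of confounding.
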